#### Process evaluation

We will triangulate multiple data sources to examine elements of fidelity, coverage and uptake, sustainability, and acceptability as well as capturing how the social, cultural and political context has affected implementation, as described below:

##### Fidelity

We will conduct (1) observations of all the government and parent meetings, spot check observations of WASH facilities pre, immediately post then 12 months post intervention, and observations of 20 Femme-led workshops sessions with girls (n=10), boys (n=8) and teachers (n=2); and (2) we will conduct unstructured informal interviews with the Femme facilitation team to assess how training went and to what degree actual implementation of each component varied from what was planned. Modifications in activities, frequency or timeline will be captured.

##### Coverage and uptake

We will capture the number of participants reached through the different intervention components, stratified by student/teacher, sex and age. This information will be collected by the Femme monitoring tool and verified during evaluators’ observations of a sample of the sessions.

##### Sustainability

Unannounced WASH spot check observations will be conducted at two time points post intervention by the MITU team (7 and 12 months), which will be in addition to the routine monitoring and evaluation by the Femme implementation team (6 and 12 weeks). All observations of the WASH facilities will use an adapted observation checklist (see table 2).

##### Acceptability

Acceptability of the intervention will be assessed using two FGDs per school with up to 10 girls and 10 boys who received the intervention, at two time points, months 1 and 12 post intervention. The students will be randomly sampled from a list of all those who attended the intervention sessions. Additionally, three KIIs will be conducted with teachers and two KIIs per district with district officials at these same time points, to assess the acceptability of the school intervention.

##### Context

Social, cultural, political and logistical factors that may have facilitated or inhibited the implementation of the intervention will be explored using IDI and FGD among students and teachers from school interventions at the end of the intervention at 12 months. Contextual reasons for adaptations to the intervention and its delivery will be also explored.

## Economic evaluation

A costing study will be conducted to estimate the total costs of developing, setting up and running the intervention. A combination of top-down and ingredients-based costing approaches will be used to generate cost estimates for the whole intervention, and for each component. All costs will be estimated from the societal perspective (the students, the schools and implementing partners) and financial and economic costs will be calculated for all inputs. Costs will be collected using accounting records, staff time survey and process evaluation data including interviews with participants. Capital costs and those costs with a lifespan greater than the project life will be annualised over their useful life. Costs will be entered into an Excel-based costing tool. The cost analysis will describe the distribution of costs across different forms of inputs, and will estimate the unit cost per student reached, the cost of delivering all activities in schools, and the cost per unit of measure for selected intervention outcomes. The cost estimate will be compared with similar school programmes in the region and will inform programme replication, scalability and financial sustainability for different implementing partners.

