### Phase II: pilot implementation of the intervention

#### Sampling strategy

The District Education Officers (DEOs) will provide a list of mixed-sex secondary schools from two districts in Mwanza region (as agreed on in the formative phase). A shortlisting will be conducted based on student enrolment (targeting mid-sized schools enrolling between 125 and 140 girls in Forms 2 and 3), location (to include both urban and peri-urban schools), proximity to Mwanza city, and both day and boarding mixed-sex schools where possible. A random sample of four schools will be obtained from the shortlisted schools.

In each school, all girls in Forms 2 and 3 who assent to participate and a random sample of 50 male students enrolled in the same classes as the girls, will be invited to join a longitudinal cohort study, within which we will administer a pre and post intervention assisted self-completed paper-based survey (as described above). We determined that 500 girls—each participating in the baseline and end line survey—were required to provide 80% power to detect a difference of 0.075 points in the Menstrual Practice Needs Scale (MPNS-36) questionnaire assuming a total MPNS mean score of 1.82 (SD 0.37) at baseline^22^; a two-tailed test at 5% significance level; and allowing for an intracluster correlation of 0.05% and 20% loss to follow-up between baseline and end line surveys.

In addition, we will obtain a random sample of 10 girls in each school from the participants in the female cohort who reported in the baseline questionnaire to have missed two or more days of school during and because of their last menstruation to qualitatively assess changes in school participations and experiences of the intervention. We will also purposively select two staff in each school based on individual involvement in MSRH issues within the school to participate in KIIs (see table 1 for more details).

No participants will receive monetary incentives. All will receive MSRH education and workbooks; girls will receive a kit containing, among other things, a reusable menstrual product.

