### Intervention delivery and components

The intervention will be delivered by Femme after refinement during the formative phase. The evaluation will be conducted by a MITU/LSHTM team (see figure 2). The following components are expected to be part of the finalised intervention:

**Comprehensive education sessions** will be delivered by Femme facilitators immediately following regular school activities to all Form 2 and 3 girls and boys (~500 girls and ~500 boys, age range 14–18 years) in four schools. Ideally sessions will run over 5 days and last approximately 1–2 hours per session; however, this may vary by school depending on their timetable and availability. In each school, girls and boys will first be together for two sessions covering anatomy, puberty, virginity, relationships and gender roles, basics of menstruation, reproductive health and pregnancy. Two subsequent boys’-only sessions will cover hygiene, physical (sexually transmitted infections, urinary tract infections) and mental (anxiety, substance abuse) health, gender-based violence and relationships. Three girls’-only sessions will cover hygiene, menstruation (management, reusable products), pregnancy, physical health (RTIs, STIs, UTIs), anxiety and pain management. The formative phase will inform about the frequency and distance between sessions.

**Menstrual pain management** will likely include the provision of strategies such as application of heat, dietary options, mild exercise/stretching, recommendations for over-the-counter analgesics such as Panadol or Ibuprofen, and incorporate anxiety-reducing and pain-reducing breathing techniques during the girls only sessions. During the formative phase, we will also explore (with the schools and LGAs) the best way for such analgesics to be made available and dispensed within the schools.

**Distribution of reusable menstrual products** (menstrual cups, reusable pads, period underwear). During the girls’-only sessions, students will be taught the advantages, disadvantages and usage of all products. At the end of the education sessions, girls will receive a Femme kit. If deemed appropriate during the formative phase, a boy’s kit will be developed and delivered in the pilot, such a kit could include information booklets, soap in a container, underwear.

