### Current status

At the time of publication, the formative phase and preliminary government engagement will be finished. Phase III implementation begins in January 2022 and ends in January 2023.

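### The annualisation rule does not separate assets that are kept from items given away, so a reusable product that outlasts the project may enter the cost per student at only part of its price

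*Protocol article*

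**What the plan says.** The Economic evaluation section sets one rule for long-lived inputs: "Capital costs and those costs with a lifespan greater than the project life will be annualised over their useful life". It says that "financial and economic costs will be calculated for all inputs", and does not say whether annualisation applies to one of these cost types or to both. The analysis "will estimate the unit cost per student reached, the cost of delivering all activities in schools", and the resulting estimate "will inform programme replication, scalability and financial sustainability for different implementing partners". Cost per student is also named under feasibility in the study objectives.

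The intervention includes items that leave with the recipient. Under Sampling strategy, "girls will receive a kit containing, among other things, a reusable menstrual product". Under Intervention delivery and components, the products are listed as "menstrual cups, reusable pads, period underwear", and "At the end of the education sessions, girls will receive a Femme kit". Female teachers also receive a reusable product. The same section describes small WASH improvements, such as door locks and hooks, which remain at the school.

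The article does not define project life. The Current status section dates implementation only: it "begins in January 2022 and ends in January 2023".

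**The concern.** Annualising spreads the cost of an asset over the years in which it serves the programme. That suits a door lock, which next year's students will also use. A cup, a set of reusable pads or a pair of period underwear serves one girl, and the next cohort needs new ones. The rule asks only whether the item outlasts the project. It does not ask who keeps it, and it makes no exception for items given away.

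Dividing an annual share of the product by the number of students, each of whom is reached once, mixes two bases. The numerator is a cost per year of use and the denominator is a count of new recipients. The result is not the money needed to reach one more student. A district or NGO that budgets a new cohort from it would plan for too little product cost.

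**Working it through.** The article states no cost figure, so there is nothing to reproduce. The check has two parts: which items the rule reaches, and how far the charge could fall short under assumed inputs.

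**Which items the rule reaches**

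| Item | Who keeps it | Serves the next cohort? | Annualised under the rule as worded? |
|---|---|---|---|
| Door locks, hooks | School | Yes | Yes, if it outlasts the project |
| Reusable product in the girl's kit | The girl | No | Yes, if it outlasts the project |
| Reusable product for a female teacher | The teacher | No | Yes, if it outlasts the project |

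The last column is the same in every row, although the third column differs.

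**Share of the price charged**

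Assumed inputs, none of them in the article: product life L of 1 to 10 years and discount rate r of 0% or 3%.

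One annual share = 1/L with no discounting, or r / (1 − (1 + r)^−L) with discounting.

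- L = 1: 100% at either rate, so no effect.
- L = 2: 1/2 = 50%; at 3%, 0.03 / (1 − 1.03^−2) = 0.523, or 52%.
- L = 5: 1/5 = 20%; at 3%, 0.03 / (1 − 1.03^−5) = 0.218, or 22%.
- L = 10: 1/10 = 10%; at 3%, 0.03 / (1 − 1.03^−10) = 0.117, or 12%.

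Project life may exceed the implementation year. If two annual shares are charged (straight line, 2/L), the share is 100% at 2 years, 40% at 5 years and 20% at 10 years.

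**Effect on the unit cost**

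Let s be the product's share of the full unit cost (assumed 10%, 30% or 50%). With one straight-line share, annualised unit cost ÷ full unit cost = (1 − s) + s/L.

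| Life | s = 10% | s = 30% | s = 50% |
|---|---|---|---|
| 2 years | 95% | 85% | 75% |
| 5 years | 92% | 76% | 60% |
| 10 years | 91% | 73% | 55% |

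For example, with s = 30% and L = 5: 0.70 + 0.30/5 = 0.76. If two shares are charged, the 2-year row becomes 100% throughout, and the 5-year row becomes 94%, 82% and 70%.

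Over these ranges the shortfall runs from nothing to about 45% of the unit cost. The upper end needs a 10-year life, a single annual share and a product that makes up half of the full cost.

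**The case against.** The strongest reply is that no error has been shown. The article does not class the kit as capital, gives no useful life for any product, and lists three product types whose lives may differ. Item classification, useful lives and discount rates are commonly left to a fuller costing plan. Financial costs are planned alongside economic costs and draw on accounting records, so the full kit outlay may appear there. Costs are also planned by component, and product distribution is a named component, so a careful reader might recover the figure. Finally, annualising long-lived items is ordinary practice, and an annualised product cost is a legitimate answer to a different question: the cost per year of use.

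Most of this stands, and it limits the point. A reader might infer that the product is bound to enter at a one-year share and that the reported unit cost is therefore understated. The article does not support that: project life is undefined, more than one share may be charged, and the financial costs may already carry the full price. A reader might also infer that annualising makes reusable products look unfairly cheap beside consumables. That does not follow, because a year's share of a reusable product against a year's supply of consumables is a like-for-like comparison if the girl uses the product over its life. Nor does the single unit cost for girls and boys amount to a fault. Component costs, together with reach recorded by sex (Coverage and uptake), allow separate figures to be derived.

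The reply does not remove the wording itself. The article states the inclusion test, and that test depends on lifespan alone. It is not limited to economic costs. The missing useful lives are detail that a fuller plan can supply, but the stated rule does not fit the output it feeds.

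**Conclusion.** The point holds conditionally. As worded, the rule covers items handed to one recipient as well as retained assets. If a product outlasts the project and the rule is applied literally, the cost per student reached carries only part of the product's price and understates the outlay per new student. The size cannot be established from the article. The shares of 52%, 22% and 12% rest on assumed lives of 2, 5 and 10 years, 3% discounting and a single annual share. The effect is zero for a product that does not outlast the project. It is also absent from any reported figure that already carries the full outlay. This is a cheap improvement to a stated rule, and not a demonstrated error in a result.

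**What to change.** Amend the rule in the Economic evaluation section as follows:

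- In the cost per student reached that is used for replication and budgeting, count items given to students or teachers at full acquisition cost in the year of delivery.
- In that figure, annualise only assets that the school or programme retains.
- Report any figure that annualises the product alongside it, labelled as cost per student-year.

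No new data collection is needed. The cost is one extra reported line and, where the product outlasts the project, a less favourable unit cost.

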### Data management and analysis

#### Quantitative data

The quantitative survey data will be entered into customised MySQL databases and transferred to STATA V.15 (Stata Corp College Station, Texas, USA) for cleaning and analysis. Paper source documents will be stored in lockable cabinets within the data room at MITU which is locked and accessed by data mangers only. Electronic data will be stored on servers at MITU. Descriptive analysis will be conducted with baseline data using mean (SD) or median (range) to summarise continuous variables. Similarly, frequency and percentages will be used to describe participants’ characteristics collected using categorical variables. The effect of the intervention on the primary outcome of MPNS—a continuous outcome—will be assessed with random-effects linear regression model adjusting for baseline measure, and including individual as a random effect and school as a fixed effect. For binary secondary outcomes, random-effects logistic regression will be used to estimate adjusted ORs with random effects for individuals to account for within-individual clustering of baseline and end line responses.

#### Qualitative data

Detailed field notes will be taken by a research assistant; additionally FGDs, KIIs and IDIs will be recorded using digital voice recorders. Immediately post data collection the research assistant and study coordinator will use the field notes and recordings to prepare detailed field notes. Additional post data collection debrief meetings will take place after every 2 days of data collection between the data collection team (RA and study coordinator) and one of the study principal investigators. Immediately post data collection the research assistant and study coordinator will use the field notes, recordings and debrief meetings to prepare analytical memos at the individual interview/FGD and then school level. The recordings will then be transcribed then translated and stored in an interoperable document file format (*.odt) recommended for long term preservation. A thematic analysis approach will be used, which will include the following steps: (1) grouping of the statements and words according to similarity in meaning; (2) we will then apply codes (meaningful labels) to the groupings; and then (3) we will group the codes into categories (codes), which are eventually grouped into themes. We will employ grounded theory principles of constant comparison, theoretical sampling and saturation, and analytical memo writing during data collection and analysis. NVivo shall be used during data analysis. We will maintain rigour through ongoing discussion within the research team regarding each step of the research process and the resultant interpretations from the data. We will use verbatim quotes to support our interpretations of the data and pay close attention to disconfirming cases and divergent views of the participants. Lastly, we will present preliminary study findings to the intervention team and the district facilitation team to discuss and reach consensus on the interpretation and the way in which we have represented the study findings.

### Ethics and dissemination

All participants will provide written informed consent. Head teachers will provide overall consent on behalf of adolescents aged below the age of 18 years before they give assent. Each participant will be informed that participation in the study is voluntary and that they are free to withdraw, without justification, from the investigation at any time without consequences. Information about the aims of the study and its methods will be provided to the participants before asking for their written informed consent or assent to participate in an interview or FGD. If the respondent has agreed for the interview to be recorded, then the consent procedure will be digitally recorded using handheld devices. Each respondent will be assured of the confidentiality and privacy during data collection, management and analysis of data. All interviews will be conducted in private, out of ear shot of other persons. All information from the respondents will be kept confidential. Personal data will be anonymised using ID numbers, and stored data will be stripped of names, and password protected for use by named research staff only.

We envisage minimal risk should a girl be ‘seen with a Femme Kit’. Our project aims to demystify and de-stigmatise menstruation. In partnership with multiple stakeholders (teachers, parents, boy and girl students), project activities include developing school-level action plans to create a supportive environment. All participants will benefit from increased knowledge and understanding of both their own body and how it works, as well as that of the opposite sex. Additionally, female teachers and students will benefit from improved menstrual management strategies (including pain reduction, anxiety reduction) and a reusable menstrual product. The intervention is hypothesised to reduce menstrual-related stigma through provision of education and stakeholder engagement. All participants will be given information about local SRH services at the end of their interview. Precautions will be taken to control and modify potential discomfort, distress or hazards to research participants.

Participants will not be paid for taking part in the study. The only payments made to participants will be to compensate for travel costs for those who will have to travel in order to participate in the study. Participants who will take part in the stakeholders’ meetings and FGDs will be given refreshments during the meetings/FGDs.

Protocol, tools and consent have been reviewed and approved by the independent Tanzanian national ethics committee (Ref: NIMR/HQ/R.8a/Vol.IX/3647) and LSHTM ethical review board (LSHTM Ethics Ref: 22 854).

Our dissemination plan allows for flexibility to be responsive to any contextual changes. Our targeted audiences are both academics and non-academic audiences. Our dissemination plan will form part of the overall pathway to impact plan for the project. Local and national stakeholders will be involved throughout the life of the project starting with involvement during the refinement of the intervention. Study findings will be disseminated to local stakeholders through presentation in relevant stakeholders’ meetings such as the Tanzania Menstrual Health Day, and sharing key findings through webinars and social media. We will also share study findings in relevant international conferences and publish in open-access peer-reviewed journals.

### Current status

At the time of publication, the formative phase and preliminary government engagement will be finished. Phase III implementation begins in January 2022 and ends in January 2023.
